To date, a number of small observational studies have identified perturbations in creatine homeostasis in preterm infants (Blüml et al., 2014; Koob et al., 2016). Koob et al. (2016) reported that at term CPA creatine concentrations in the centrum semiovale of infants born preterm (born 29.1 ± 2 weeks) were reduced compared to those born at term (Koob et al., 2016). In addition, Lage et al. (2013) found that by hospital discharge, preterm infants had higher urinary GAA and reduced urinary creatine excretion, suggesting differences in systemic creatine synthesizing capacity. This was particularly apparent in their very preterm group (28–29 weeks) (Lage et al., 2013).

No studies have characterized longitudinal changes in creatine metabolism among preterm infants or the association between cerebral creatine content and neurodevelopmental outcomes. Further to this, no studies have monitored systemic creatine levels (both circulating and excreted) in a single preterm population nor have they assessed nutritional creatine availability for preterm infants fed with total parenteral nutrition (TPN), preterm infant formulas, or breast milk.

We hypothesize that following preterm birth, peripheral and cerebral creatine levels will fall, so that at term CPA, preterm infants will have relative systemic and cerebral creatine deficiency. Furthermore, this reduction in creatine bioavailability will jeopardize normal brain metabolism and development, ultimately predisposing the infant to neurodevelopmental dysfunction.

The overall aim of this study is to assess whether preterm infants become creatine deplete in the early postnatal period, by measuring the preterm infants’ circulating and excreted levels of creatine and GAA and comparing these measures to cerebral creatine content, as determined by ^1^H-MRS, at term corrected age. This study will correlate preterm creatine levels with neurological outcomes using MRI, general movements assessment (GMA), and the Developmental Assessment of Young Children – Second Edition (DAYC-2) Test (Novak et al., 2017). This study will also establish the levels of creatine provided through dietary intake during the days and weeks after preterm birth. Results of this study may support the use of creatine supplementation as standard nutritional care of the preterm infant, in order to improve neurodevelopmental function in this vulnerable population.

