### Specific Aims

Compare cerebral, plasma, and urine creatine and GAA content between preterm and term infants at CPA.Describe preterm infant plasma and urine creatine and GAA concentrations and creatine:GAA ratio in the early postnatal period.Describe associations between cerebral creatine content, plasma, and urine creatine concentrations with maternal and infant characteristics at CPA.Compare creatine, GAA, arginine, glycine, and methionine concentrations in standard preterm nutrition, including TPN, preterm infant formulas, and breast milk.Determine whether dietary source of creatine (TPN, formula, or breast milk) is related to plasma or urine creatine concentrations in the early postnatal period.Describe associations between cerebral creatine content and blood and urine creatine concentrations with neurological outcomes (GMA, MRI, and DAYC-2) at CPA and at 3 months of corrected postnatal age.

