### Sample and Data Collection

#### Blood, Urine, and Nutrition Sampling

A schematic overview of the sampling regime for each participant is outlined in Figure 1. At the time of birth, we will use a finger prick to collect ~120 μl of maternal whole blood using a capillary tube. A 2-ml venous cord blood sample will also be collected from which a ~120 μl sample will be obtained using a capillary tube. Then, while infants are receiving care in the NICU, or on postnatal wards, and at follow-up appointments, the following samples will be collected. Sample frequency will be dictated by gestational age at birth.

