**Figure 1 fig1:**
[figure not shown]
Schematic representation of UNICORN sampling regime. Samples of neonatal blood, urine, and nutrition will be collected weekly or bi-weekly for the duration of the infants stay in hospital. Magnetic resonance imaging (MRI) and magnetic resonance spectroscopy (^1^H-MRS) will be performed at term corrected postnatal age (CPA). Infants will also undergo a general movements assessment (GMA) at CPA and at 3 months CPA. At the follow-up appointment at 3 months CPA, further neurological assessment will be completed using the Developmental Assessment of Young Children – Second Edition (DAYC-2) assessment tool.

**Blood sampling**: A blood sample will be collected biweekly. We will perform a heel prick to collect ~120 μl of whole blood using a capillary tube. All blood samples (cord, maternal, or infant) will be transferred to a Hemaspot™ SE blood separation device to facilitate collection of the cell-free blood fraction (referred to throughout as plasma for clarity) from a small volume of whole blood. Hemaspots are allowed to dry at room temperature before being stored at −20°C for future analysis.

**Urine sampling**: Around the same time as the blood collection, and on each alternate week, we will place some gauze into the infant’s nappy to facilitate a spot urine collection. Once obtained, this sample will be transferred to an Eppendorf tube and stored at −80°C for future analysis.

**Nutrition sampling**: A 200 μl sample of the nutrition (TNP, formula, and breast milk) being fed to each infant at the time of the blood and urine sampling will be collected. If in powdered form (formula), this will be reconstituted following standard practices. All samples will be transferred into an Eppendorf tube and stored at −80°C for future analysis.

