### Statistical Analysis

Characteristics of the population will be tabulated, along with appropriate descriptive statistics of the study sample. Continuous data will be assessed for normality and expressed as means and standard deviations or median and interquartile range as appropriate. Categorical data will be expressed as counts and proportions. Average creatine content from nutrition per week for each baby in the early postnatal period will be calculated.

Differences in creatine and GAA measures (^1^H-MRS, plasma or urine) between infants born preterm and those born at term will be assessed at CPA using a t-test or Mann-Whitney U test as appropriate. The correlation between gestational age at birth and creatine and GAA measures at CPA will also be determined using a Spearman or Pearson correlation. Preterm infant plasma and urine creatine and GAA concentrations and creatine:GAA ratio in the early postnatal period will be described and plotted. Associations between cerebral creatine content, plasma and urine creatine concentrations with maternal, and infant characteristics at CPA will be determined using Spearman or Pearson correlations for continuous data (maternal age, gestational age, birth weight, parity, gravity, placental weight) or a t-test or Mann-Whitney U test for categorical data (infant sex, mode of delivery, maternal comorbidities, country of birth, ethnicity, and dietary preferences), as appropriate. Differences in creatine, GAA, and amino acid content of nutrition sources (TNP, formula or breast milk) will be determined using a one-way ANOVA or Kruskal-Wallis H test as appropriate. The association between creatine, GAA, and amino acid content of nutrition sources (TNP, formula or breast milk) and infant plasma and urine creatine at CPA will be assessed using a Spearman or Pearson correlation as appropriate. Finally, the association between cerebral creatine content, plasma creatine levels, and the ratio of plasma:cerebral creatine at CPA with GMA, MRI global injury, and DAYC-2 scores will be determined using linear regression at both CPA and at 3 months’ corrected postnatal age. Potential confounders such as gestational age and maternal and infant characteristics will be assessed, along with collinearity, prior to performing multivariable linear regression.

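### The hypothesised fall in creatine after preterm birth is described and plotted but never estimated within infants, and the cord-blood value enters no named analysis

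*Protocol article*

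**What the plan says.** The Introduction states the hypothesis as a change over time with an end state: "We hypothesize that following preterm birth, peripheral and cerebral creatine levels will fall, so that at term CPA, preterm infants will have relative systemic"; the sentence then names a shortage in the brain as well. Primary Outcome Measures lists plasma and urine creatine and GAA from birth to discharge and again at CPA. The matching item under Specific Aims is "Describe preterm infant plasma and urine creatine and GAA concentrations and creatine:GAA ratio in the early postnatal period".

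On sampling, the Figure 1 legend says "Samples of neonatal blood, urine, and nutrition will be collected weekly or bi-weekly for the duration of the infants stay in hospital". The section on blood, urine and nutrition sampling adds that frequency depends on gestational age at birth. For a value at birth, "A 2-ml venous cord blood sample will also be collected", and cord samples go onto the same blood separation device as the infant samples.

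The Statistical Analysis section treats the serial data in one sentence: "Preterm infant plasma and urine creatine and GAA concentrations and creatine:GAA ratio in the early postnatal period will be described and plotted". The end state gets formal analysis. Differences in creatine and GAA measures "between infants born preterm and those born at term will be assessed at CPA using a t-test or Mann-Whitney U test as appropriate", and "The correlation between gestational age at birth and creatine and GAA measures at CPA will also be determined using a Spearman or Pearson correlation". Every other test or regression named there that uses infant plasma or urine also takes the value at CPA. Cord blood is not mentioned in that section.

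**The concern.** The article's central idea is depletion after birth, and it presents the lack of longitudinal data in preterm infants as the gap it will fill. The serial samples are the only data that can show depletion, yet they produce no estimate and no interval. Two consequences follow.

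- **The cause of a low CPA value stays open.** Infants may have fallen after birth, or may have been low at birth and stayed there. These have different implications for the supplementation trial that the Discussion says this study should inform.
- **The plots carry the whole weight of the claim.** The later postnatal weeks come increasingly from the least mature infants, because they stay longest. A curve averaged over all infants by postnatal age would mix change within infants with change in who is still being sampled.

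**Working it through.** **1. Match each part of the hypothesis to its data and its analysis.**

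| Part | Data collected | Analysis named |
|---|---|---|
| Lower than term infants at CPA | MRS, plasma and urine at CPA | t-test or Mann-Whitney U; correlation with gestational age |
| Plasma falls after birth | Cord blood, serial heel-prick samples, CPA sample | Description and plots |
| Urine course after birth | Serial spot urine, CPA sample | Description and plots |
| Cerebral creatine falls after birth | One MRS scan, at CPA | None possible |

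**2. What the CPA comparison can show.** For any infant, value at CPA = value at birth + change since birth. Take a hypothetical scale with term infants at 100. Infant A starts at 100 and loses 10; infant B starts at 90 and loses nothing. Both are at 90 at CPA, 10 below term. The CPA comparison treats them alike. The cord value would separate them for plasma.

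**3. The plan's own figure.** The Sample Size section aims for 20 per group, citing a study with 13 preterm infants, 20-25% scan failure and 20% loss to follow-up. 13/(1 − 0.20)/(1 − 0.20) = 20.3, and 13/(1 − 0.25)/(1 − 0.20) = 21.7, so 20 is approximately reproduced. It rests on cerebral creatine at CPA and says nothing about precision for change over time.

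**4. Pooled average with every infant flat.** Assumptions, none from the article: equal groups at mid-band gestations of 25, 28.5, 31.5 and 35 weeks, serial sampling until 37 weeks, and constant levels within infants. A group contributes while gestation + postnatal weeks ≤ 37. Levels are listed from least to most mature group.

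| Postnatal week | Groups contributing | Levels 80/87/93/100 | Levels 100/93/87/80 | All 90 |
|---|---|---|---|---|
| 0 | 4 | 90.0 | 90.0 | 90.0 |
| 4 | 3 | 86.7 | 93.3 | 90.0 |
| 6 | 2 | 83.5 | 96.5 | 90.0 |
| 10 | 1 | 80.0 | 100.0 | 90.0 |

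The first gradient gives an apparent fall of (90 − 80)/90 = 11.1%. A milder one, 83/87/91/95, gives (89 − 83)/89 = 6.7%. The reversed gradient gives a false rise, and no gradient gives no artefact.

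**5. Adding the CPA sample.** At 40 weeks, CPA comes 40 − 25 = 15 weeks after birth for the least mature group and 40 − 35 = 5 weeks for the most mature. The extra sample therefore returns each group to the curve once, but the far end still belongs to the least mature. This was simulated with 20 infants in each of the four preterm bands, flat true profiles, between- and within-infant SD of 10, discharge at 35-37 or 36-39 weeks, and sampling every 0.5 or 2 weeks to cover both readings of biweekly.

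| Levels 80/87/93/100 | Pooled slope per week | Week 8 onward vs first week |
|---|---|---|
| Without CPA sample | −0.84 to −0.99 | −8.7% to −10.2% |
| With CPA sample | −0.53 to −0.76 | −7.1% to −8.6% |

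The within-infant slope was about 0.00 throughout. With the gradient reversed, the late samples were 6.9% to 10.3% higher. With equal levels the difference was at most 0.4%. Plotted against postmenstrual age, the sign of the pooled slope reverses.

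**6. What a within-infant estimate could detect.** For a paired change, two-sided 0.05 and 80% power, the detectable mean change in SDs of the differences is (1.960 + 0.842)/√n. This is 0.31 for n = 80 (all preterm infants) and 0.63 for n = 20 (one group), before any losses.

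**The case against.** The strongest reply is that aim and analysis agree. The aim is to describe the postnatal course, the outcomes are called mainly descriptive, and describing and plotting does that. The Discussion frames the expectation against an infant of the same postconceptional age, which is a between-infant contrast tested at CPA. An unseen analysis plan may contain a longitudinal model.

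Part of this stands. A reader might infer that the central hypothesis is untested, but its end state is formally compared with term infants and related to gestational age. A reader might also infer that sampling stops at discharge; a further sample is taken at CPA. Nor does the article say that the plots will be pooled. The design is stratified by gestation and age is recorded at each sample, so plots by group or per infant would largely avoid the artefact. The percentages above show what is possible, not what is likely, and their direction depends on an assumed gradient.

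The main point survives. The Statistical Analysis section does not defer the serial data to another document; it chooses an analysis for them, and that analysis does not quantify the change in the hypothesis. A mean within-infant change with its interval is itself descriptive, so the descriptive label does not exclude it. The Discussion also says the data will allow effect sizes to be calculated for future studies. The CPA comparison supplies a group difference, but nothing planned supplies an effect size for the fall.

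**Conclusion.** The concern holds for the postnatal fall, not for the hypothesis as a whole. As written, the plan can show whether preterm infants are lower at CPA, but not whether they became so after birth, although the plasma data to address this will be collected. That conclusion rests only on the article's text.

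The risk of a misleading plot is conditional. It needs pooling by postnatal age and levels that differ by gestation. Under the assumptions shown it amounts to about 7-10% in either direction with no infant changing, and it persists at 7-9% with the CPA sample included. The documents do not support saying that a plotted fall would be an artefact. They support only saying that the named analysis does not guard against one.

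The cerebral part of the fall cannot be estimated by any analysis, because there is a single scan. The point is worth acting on and does not invalidate the study.

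**What to change.** In the Statistical Analysis section:

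- Add a linear mixed model for log plasma creatine, GAA and their ratio, with a random effect per infant and postnatal age by gestational group. Use the cord value as time zero, or the first infant sample if cord and heel-prick values are not comparable.
- Fit the same model for urine with the first urine sample as the starting point, since there is no cord equivalent.
- Report the within-infant change to CPA for each gestational group with a 95% confidence interval. Keep the time terms simple where infants have few samples, as late-preterm infants may.
- Plot by gestational group and show the number of infants contributing at each age.
- State that a cerebral fall cannot be estimated from one MRS scan and that the MRS comparison addresses the level at CPA only.

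Adjusting the preterm-versus-term comparison at CPA for cord creatine is not advised. The cord value precedes CPA by about 15 weeks in an infant born at 25 weeks but is almost contemporaneous in a term infant. It may also vary with gestation, so adjustment could remove part of the contrast of interest.

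The cost is modest extra analysis of samples already planned. With about 20 infants per group the intervals may be wide, and the report should say so.

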Creatine is a metabolite essential for brain development and energy metabolism (Braissant et al., 2007). It is an amino acid derivative that fuels the creatine kinase circuit; a phosphagen system that mitigates temporal imbalances in energy (ATP) supply and demand (Wallimann et al., 1992). *Via* the creatine kinase circuit, creatine and its phosphorylated derivative (phosphocreatine, PCr) shuttle high-energy phosphate groups from the mitochondria into the cytosol, for the regeneration of ATP from ADP (Ellington, 2001). The creatine kinase isoforms required to run the circuit are found in the cerebellum, choroid plexus, hippocampal granular layer, and pyramidal cells of the brain (Hemmer et al., 1994) and are involved in maintaining ATP homeostasis in the central nervous system (CNS) from early in embryonic development through to adulthood (Braissant et al., 2001; Braissant et al., 2007).

Both creatine and phosphocreatine are spontaneously broken down into creatinine at a rate of ~1.7%/day (Brosnan and Brosnan, 2007). Thus, there is a requirement to replenish creatine and PCr stores on a daily basis. Creatine can be obtained from the diet and is also endogenously synthesized *de novo*. Synthesis involves the production of guanidinoacetate (GAA) from arginine and glycine, in a reaction catalyzed by arginine:glycine aminotransferase (AGAT) that occurs predominately in the kidney and pancreas. GAA is then methylated by guanidinoacetate N-methyltransferase (GAMT), mainly in the liver, to produce creatine. Once synthesized or absorbed, creatine is transported into cells *via* the sodium-dependent SLC6A8 creatine transporter (Wyss and Kaddurah-Daouk, 2000). Creatine is able to cross the blood-brain barrier (Ohtsuki et al., 2002), and the brain itself also has some inherent capacity to synthesize creatine, with both AGAT and GAMT expressed by neurons, astrocytes, and oligodendrocytes (Braissant et al., 2001; Tachikawa et al., 2004; Nakashima et al., 2005). Despite the importance of creatine for brain growth and development, the relative importance of cerebral creatine derived from systemic rather than local synthesis has not yet been established.

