*In utero* fetal magnetic resonance spectroscopy (^1^H-MRS) studies indicate cerebral creatine accretion occurs from 18 to 40 weeks of gestation (Evangelou et al., 2015). Postnatal studies have also clearly identified that an increase in cerebral creatine concentration occurs during the first 3 months of life (Blüml et al., 2012; Blüml et al., 2014). The importance of a maternal source of creatine for the developing fetus and the continued postnatal accretion of cerebral creatine is made evident by those infants diagnosed with inherited creatine deficiency syndromes. These infants typically raise no concerns antenatally; however, as postnatal creatine levels fall, they become progressively more symptomatic with altered neurological state (Almeida et al., 2006) and complex neurological symptoms including impaired psychomotor development, seizures, and cognitive impairment (Battini et al., 2006).

In adults, creatine is acquired *via* the diet and *de novo* synthesis, with each contributing ~50% (Brosnan and Brosnan, 2007). However, in infancy, due to low levels of creatine in human breast milk and commercial formulas, a term infant most likely synthesizes between 64 and 93% of their daily creatine requirements (Edison et al., 2013). The age at which a fetus/newborn develops the capacity to synthesize creatine is currently unknown, but it requires sufficient renal, hepatic, and cerebral maturity to express the enzymes necessary for creatine synthesis. Evaluation of AGAT and GAMT expression in the rat embryo found that AGAT was expressed in isolated cells of the CNS from 0.6 gestation; however, widespread expression of AGAT and rudimentary GAMT expression were not apparent before 0.8 gestation (Braissant et al., 2005). Our own studies in the precocial spiny mouse found that the fetal kidney and liver do not express AGAT and GAMT before 0.9 gestation, an age and maturation equivalent to ~35 weeks’ human gestation (Ireland et al., 2009). Taken together, these observations raise compelling questions about progressive creatine depletion in preterm infants, and whether this complication of nutritional compromise predisposes or compounds their risk of altered cerebral metabolism and thus long-term neurodevelopmental disability.

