### Recruitment

We will recruit infants at gestational ages 23^+0^–26^+6^, 27^+0^–29^+6^, 30^+0^–32^+6^, 33^+0^–36^+6^, and 39^+0^–40^+6^ weeks. We will aim to capture 20 infants at each time point (with equal numbers of males and females). Eligible infants will be identified based on gestational age at delivery and consideration of inclusion and exclusion criteria. Pregnant women will be approached at presentation to Delivery Suite to discuss study participation. If consent is obtained, the mother and infant will be recruited to the study and the consulting obstetric, midwifery, neonatal, and nursing team advised of their involvement. Where pre-delivery consent is not obtained due to rapidity of labor and/or other clinical factors, cord blood will be collected preemptively, and retrospective consent and maternal blood sample sought within 24 h of delivery. If the parents do not wish to participate, the cord blood sample will be disposed of using routine clinical biological waste disposal systems and no further study samples collected.

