#### MRI/^1^H-MRS Data Acquisition

At 40 weeks of corrected postnatal age (CPA), each participant will undergo a MRI/^1^H-MRS scan. MR examinations will be performed on a Siemens 3T Skyra using a 16-channel dedicated pediatric head coil. Infants will be examined without sedation using a “feed and wrap” technique according to standard institutional practice. In brief, infants are brought to the MRI unit, fed, and swaddled comfortably while being monitored with continuous pulse oximetry before being placed in the MRI scanner. Standard, size appropriate, hearing protection will be used for all infants. Sequences will be performed to demonstrate brain anatomy and will include T1 3D 1 mm volumetric, T2 1 mm 3D volumetric scans, T2 TSE FLAIR, and T1SE MTC sequences. These sequences will also contribute to the analysis of any detected brain pathology. T2 SWI axial images will be performed to show calcification and blood products. Sequences for the detection of vascular injury and infarction will include diffusion sequences (b value = 2000), resting BOLD, and arterial spin labeling. ^1^H-MRS will provide chemical spectra of the brain to further analyze brain pathology and measurement of cerebral creatine content. For MR spectroscopy, the voxel will be placed over the white matter underlying the central sulcus within the centrum semiovale and spectra acquired with a long echo time (TE 135 ms) (Koob et al., 2016).

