## Discussion

Both creatine and the creatine kinase circuit are critical for brain metabolism (Braissant et al., 2011). It is hypothesized that preterm infants will become creatine deplete in the early postnatal period, due to premature delivery from a maternal source of creatine *in utero,* limited capacity for endogenous synthesis postnatally, and a limited supply of creatine in newborn nutrition. This creatine depletion may alter cerebral creatine metabolism, contributing to or compounding the risk of neurological disability in this population.

We anticipate that preterm babies will have altered creatine homeostasis and reduced creatine accretion in the early postnatal period compared to an infant of the same postconceptional age. Whether or not relative creatine deficiency is associated with neurological deficit will be a secondary outcome of this study. As the results are mainly descriptive and a formal power calculation could not be completed, there is the possibility that sample size may become a limitation for some of the proposed analyses in this observational study. However, the data obtained will enable calculation of effect size for future studies. If our overall hypothesis is supported, this observational study will inform a future randomized control trial of infant dietary creatine supplementation following premature birth, with the aim of improving brain metabolism during a key stage of development and thereby reducing the burden of neurodevelopmental disability in this high-risk population.

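### Maternal characteristics are related to infant creatine only at term CPA, 3 to 17 weeks after a preterm birth, by pooled tests with no stated adjustment for gestational age

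*Protocol article*

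**What the plan says.** Aim 3 under Specific Aims is to "Describe associations between cerebral creatine content, plasma, and urine creatine concentrations with maternal and infant characteristics at CPA". The Statistical Analysis section follows it: "Associations between cerebral creatine content, plasma and urine creatine concentrations with maternal, and infant characteristics at CPA" are to be examined by Spearman or Pearson correlation for continuous variables (including maternal age, parity and placental weight) and by t-test or Mann-Whitney for categorical ones (including comorbidities and dietary preference). Gestational age is in the continuous list as a characteristic of its own, not as an adjustment variable. Checking of confounders is mentioned once, after the regressions of neurological outcome and ahead of multivariable linear regression.

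On timing, MRI/1H-MRS Data Acquisition states: "At 40 weeks of corrected postnatal age (CPA), each participant will undergo a MRI/^1^H-MRS scan". Recruitment states: "We will recruit infants at gestational ages 23^+0^–26^+6^, 27^+0^–29^+6^, 30^+0^–32^+6^, 33^+0^–36^+6^, and 39^+0^–40^+6^ weeks". Maternal capillary blood and venous cord blood are taken at birth (Blood, Urine, and Nutrition Sampling), but Statistical Analysis names no test for either. The early postnatal plasma and urine series is to be described and plotted.

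On mechanism, the Introduction stresses "The importance of a maternal source of creatine for the developing fetus" and says that creatine and phosphocreatine are "spontaneously broken down into creatinine at a rate of ~1.7%/day". The Discussion expects depletion "due to premature delivery from a maternal source of creatine", among other causes.

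**The concern.** Two separate weaknesses come from the stated choice of time point and test.

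**Timing.** If delivery cuts off the maternal source, as the study's hypothesis holds, pregnancy exposures such as placental weight, preeclampsia and gestational diabetes should show most clearly in creatine at delivery. The only stated test reads them at 40 weeks, after a gap of months for the earliest-born and of days or none for the term group. One pooled coefficient then averages effects at very different distances from the exposure.

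**Confounding.** The plan itself expects creatine at CPA to vary with gestational age at birth and tests that correlation separately. Any maternal variable that also varies with gestational age will inherit the association. Placental weight plausibly does. Comorbidities do so partly by design, because the term infants are to come from low-risk pregnancies while no such limit is set for the preterm infants.

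The Discussion says the data will supply effect sizes for future studies. A diluted or confounded maternal estimate would be carried into them, and a null at CPA could be taken as evidence against a maternal influence at birth.

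**Working it through.** The plan gives no figure for the lag or the dilution, so there is none to reproduce. The check uses its own inputs.

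**Inputs.** CPA = 40+0 = 280 days (MRI/1H-MRS Data Acquisition). Gestational bands from Recruitment. Breakdown rate k = 0.017 per day (Introduction).

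**Step 1: lag.** Days = 280 − gestational age at birth in days. Born 36+6: 280 − 258 = 22 days (3.1 weeks). Born 23+0: 280 − 161 = 119 days (17.0 weeks).

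**Step 2: share of the birth store left**, r = (1 − k)^days.

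| Born | Days to 40+0 | r at 1.7%/day | Mean r, 1.7% | Mean r, 1.0% | Mean r, 2.5% |
|---|---|---|---|---|---|
| 23+0–26+6 | 119–92 | 0.130–0.207 | 0.165 | 0.347 | 0.071 |
| 27+0–29+6 | 91–71 | 0.210–0.296 | 0.251 | 0.444 | 0.130 |
| 30+0–32+6 | 70–50 | 0.301–0.424 | 0.359 | 0.548 | 0.221 |
| 33+0–36+6 | 49–22 | 0.432–0.686 | 0.549 | 0.702 | 0.416 |
| 39+0–40+6 | 7–0 | 0.887–1.000 | 0.967 | 0.980 | 0.952 |

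Means weight each day in a band equally; births after 40+0 count as zero days. The 1.0% and 2.5% rates are an assumed range. The mean over the four preterm bands is 0.33 at 1.7%, 0.51 at 1.0% and 0.21 at 2.5%. The order by gestation is the same at every rate.

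**Step 3: what r does to a maternal effect.** Let a maternal factor raise the birth store by 10%, and let s be creatine supplied after birth and unrelated to the mother, as a multiple of the birth store. The relative difference at CPA is (1.1r + s)/(r + s) − 1 = 0.1r/(r + s).
- No replacement (s = 0): still 10%, whatever r is. Decay alone dilutes nothing.
- Full replacement (s = 1 − r): 0.1r, which is 1.3–2.1% in the earliest band and 4.3–6.9% at 33+0–36+6.
- Growth or accretion beyond replacement (s > 1 − r): smaller still.

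The dilution therefore depends on s, which the protocol does not give.

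**Step 4: is replacement credible on the protocol's own figures?** Sample Size cites cerebral creatine at CPA of 0.10 preterm against 0.12 term, a ratio of 0.10/0.12 = 0.83. The Introduction puts that preterm cohort at 29.1 ± 2 weeks and describes cerebral accretion from 18 to 40 weeks, so the level at birth should not exceed the term level. At 29.1 weeks the lag is 280 − 203.7 = 76.3 days and r = 0.983^76.3 = 0.27. At most 0.27/0.83 = 0.32 of the creatine present at CPA could then date from birth. If the earliest band reached the same 0.83, the bound would be 0.130/0.83 = 0.16 to 0.207/0.83 = 0.25. Most of the creatine measured was supplied later. This assumes that 1.7% per day applies to the preterm brain.

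**Step 5: consequence for a test (illustration).** Assume a 0.65 SD maternal effect at birth, equal SDs at birth and CPA, 80 preterm infants split 40/40 and two-sided 5%. Power is 83% at birth and about 17% if 0.34 of the effect remains. With 64 infants (80 × 0.8, for 20% spectroscopy failure) the figures are 74% and 14%. The effect size and the equal SDs are assumptions.

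**The case against.** The strongest reply is that the analysis matches its aim. Aim 3 is set at CPA, and so is the hypothesis of relative deficiency. A reader might infer that the plan contradicts itself, or that cord plasma should displace CPA as the main outcome for Aim 3. Neither is supported: aim and analysis agree, no aim asks about stores at birth, and cerebral creatine at term CPA is a primary outcome that cord blood cannot replace.

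A reader might also infer that maternal effects are largely washed out by CPA. The documents do not support this as a general statement. At 33+0–36+6, 43–69% of the birth store remains on the protocol's rate, and in the term group 89–100%; together these are 40 of the 100 planned infants. First-order loss alone leaves a relative difference intact. The rate is for breakdown of creatine and phosphocreatine and is not given for preterm infants, plasma or urine. The Discussion expects limited synthesis and limited supply after birth, which argues against full replacement. Maternal diet may still act through breast milk, although the Introduction calls its creatine content low. No document says that maternal age or parity act mainly through the placenta.

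Finally, this is a condensed article and the outcomes are called mainly descriptive, so an unstated cord analysis is not in itself a fault.

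All of this limits the size of the claim. It does not answer two things that the article fixes: the single late time point for a question about maternal supply, and tests pooled across gestation with no stated adjustment. The confounder sentence could be read more widely, but its placement ties it to the neurological regressions.

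**Conclusion.** The point holds as a weakness of time point and adjustment, not as an error or a contradiction. The 3-to-17-week lag is firm. Some dilution of a maternal effect present at birth is likely and is greatest in the earliest-born; the shares of 13–42% before 33 weeks and 43–69% at 33+0–36+6 are illustrations resting on the 1.7% rate and on replacement by creatine unrelated to the mother. The protocol's own preterm-to-term ratio makes substantial replacement credible without measuring it. Confounding by gestational age does not depend on the decay argument: it needs only that creatine at CPA varies with gestation, as the study hypothesizes, and that some maternal variables do too. Nothing in the article says that a null would be read as absence of maternal influence; the risk is that the plan does not guard against that reading.

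**What to change.** - Keep the associations at CPA as Aim 3, and state that those with maternal characteristics will be adjusted for gestational age at birth. Unadjusted results can stand beside them, since gestational age may lie on the path from some comorbidities to creatine.
- Add cord plasma creatine and GAA as outcomes for the same maternal characteristics, also adjusted for gestational age and labelled exploratory.
- State that a null at CPA does not exclude a maternal effect at birth.

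The cost is a change of wording and a few more exploratory tests; the cord samples and maternal data are already being collected. Two limits remain. Cord plasma is a circulating concentration and does not measure tissue or cerebral stores. Adjustment removes confounding by gestational age but does not restore an effect that has been diluted by CPA.
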